Participants can withdraw from the study at any time if they perceive poor efficacy or adverse reactions. Subjects with poor compliance, serious comorbidities or complications, or serious adverse events will be persuaded to quit the study. These subjects will be treated as drop-out cases, and the time and reason for drop-out should be stated. Once the subject drops out, investigators should try to contact the subject as much as possible to inquire about the reason and complete the assessments. The timing of the last medication should also be recorded.

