If a serious adverse event or allergic reaction happens and is of concern relative to the research medication, the emergency envelope will be opened by the principal investigator of the centre. Once opened, research on that subject will be discontinued. Then, the time and reason for the emergency unblinding will be recorded in detail in the case report form (CRF). The patient will receive corresponding standardized treatment. Simultaneously, the relevant departments, including the ethics committees of each study centre, should be informed within 24 h.

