#### Mild PD

We will use the time of the first addition of levodopa as the primary outcome for the mild PD unit to reveal the progression of the disease. When participants have a 3-point-higher UPDRS III score and have more serious symptoms, their physicians could give them levodopa or increase the dose of levodopa they were taking. The timing will be recorded at every follow-up visit or reported by the participants at any time.

Secondary outcomes will be UPDRS I–IV and total score for disease evaluation, Parkinson’s disease Sleep Scale-2 (PDSS-2), the Epworth Sleeping Scale (ESS), REM sleep behaviour disorder questionnaire (RBDSQ), Hamilton Depression Scale (HAMD), Hamilton Anxiety Scale (HAMA), scales for Outcomes in Parkinson’s disease—Autonomic (SCOPA-AUT), nonmotor symptom scale (NMSS) for assessing NMSs, Parkinson's Disease Questionnaire (PDQ-39) for evaluating QoL, and elderly quiver of TCM syndrome classification dysfunction score for TCM syndrome evaluation, uric acid (UA) and homocysteine (Hcy) for disease prognosis.

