#### Moderate PD

For the moderate PD unit, the primary outcome is the duration of the “OFF” period. The curative effect will be defined as “remission” by a ≥ 75% reduction rate, “response” for between 50 and 75%, “partial response” for between 30 and 50%, and “invalid” for below 30%.

Secondary outcomes will be Hoehn Yahr stage, Webster Clinical Symptom Scale (WCSS), UPDRSI-II for disease evaluation, Freezing of Gait Questionnaire (FOGQ) and abnormal involuntary movement scale (AIMS) to estimate MS; Wearing-off-9 Questionnaire (WOQ-9), Unified Dyskinesia Rating Scale (UDysRS), and Parkinson disease dyskinesia scale (PDYS-26) to estimate motor complications; PDSS-2, ESS, RBDSQ, NMSS, HAMD, HAMA, and SCOPA-AUT for assessing NMSs; the PDQ-39 for evaluating QoL; and the elderly quiver of TCM syndrome classification dysfunction score for TCM syndrome evaluation. UA and Hcy for disease prognosis, levodopa equivalent dose (LED), and the percentage of patients who increased their levodopa dosage will be considered in the overall response.

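### Participants with poor compliance or serious events are to be persuaded out of the study, not only off the product, which adds avoidable and possibly informative loss of outcome data in all three units

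*Protocol article*

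**What the plan says.** The rule is in the paragraph after Table 1 of the protocol article (Eligibility criteria). It is not limited to one unit.

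- Voluntary exit: "Participants can withdraw from the study at any time if they perceive poor efficacy or adverse reactions".
- Investigator-driven exit: "Subjects with poor compliance, serious comorbidities or complications, or serious adverse events will be persuaded to quit the study".
- Status afterwards: "These subjects will be treated as drop-out cases, and the time and reason for drop-out should be stated".
- Mitigation: after drop-out, "investigators should try to contact the subject as much as possible to inquire about the reason and complete the assessments". The date of the last medication is also recorded.

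The Intervention section adds a further exit route, opening the emergency envelope: "Once opened, research on that subject will be discontinued".

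Outcome collection runs well beyond most of these events. Study setting schedules visits to week 60 in the mild unit and to week 36 in the other two. For the mild unit, "We will use the time of the first addition of levodopa as the primary outcome for the mild PD unit". For the moderate unit, "the primary outcome is the duration of the “OFF” period". The advanced unit uses the PDQ-39, with infection, hospitalization and survival among its secondary outcomes. Sample size allows for 20% drop-out.

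**The concern.** The investigator-driven rule asks people to leave the study, where leaving the product would have been enough. Poor compliance, serious complications and serious adverse events can all follow randomisation. Each can depend on the assigned product, through tolerability or lack of benefit, and on the course of the disease. Compliance is checked from leftover drug at every follow-up visit, so the rule has a regular trigger, yet the article gives no threshold for poor compliance.

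At stake is the comparability of the participants whose outcomes are observed. Ordinary drop-out cannot be avoided, but this loss can, because the protocol itself instructs sites to bring it about. A statistical analysis plan can choose an analysis set and a missing-data method. It cannot recover a levodopa start date, an OFF duration or a PDQ-39 score that nobody collected.

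The advanced unit has an internal conflict as well. Hospitalization, infection and death are outcomes there, while serious events and complications are grounds for persuading the participant to leave before later ones can be observed. Safety laboratory tests and the electrocardiogram are planned only at baseline and the last visit, so early leavers may also miss the final safety assessment.

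**Working it through.** **1. The plan's own sample sizes.** Inputs from Sample size: difference and SD of 3.6 and 6.6 months (mild), 4.6 and 8.3 min (moderate), 7.3 and 8.5 points (advanced); u values 1.96 and 1.28; 20% drop-out.

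n per arm = 2[(1.96 + 1.28)·SD/difference]² + 1.96²/4

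- Mild 71.5, moderate 69.3, advanced 29.4.
- Multiplied by 1.2: 85.8, 83.2 and 35.3, rounded up to 86, 84 and 36 per arm.
- Doubled: 172, 168 and 72, total 412, as stated.

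**2. Is power the problem?** After 20% loss, 86 × 0.8 = 68.8, 84 × 0.8 = 67.2 and 36 × 0.8 = 28.8 per arm remain. Normal-approximation power at the planned effects is 89.2%, 89.5% and 90.3%. Loss of the planned size leaves power close to the 90% target, so the issue is bias.

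**3. Size of the possible bias.** The documents give no loss by arm and no outcome difference between leavers and stayers, so the following are assumptions: a fraction m of an arm is unobserved, leavers are on average k SD worse than stayers, and only observed outcomes are compared. The observed mean of that arm is then too favourable by m·k·SD. With the same k in both arms:

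bias = (m₁ − m₂)·k·SD

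All three scenarios average 20% loss over the two arms.

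| Loss by arm | k | Mild (months) | Moderate (min) | Advanced (points) | Share of planned effect | Type I error (nominal 5%) |
|---|---|---|---|---|---|---|
| 20% v 20% | any, same in both | 0 | 0 | 0 | 0% | 5% |
| 25% v 15% | 0.5 | 0.33 | 0.42 | 0.43 | 9%, 9%, 6% | 6.0%, 6.0%, 5.4% |
| 30% v 10% | 1 | 1.32 | 1.66 | 1.70 | 37%, 36%, 23% | 21%, 21%, 12% |

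Example, mild unit, last row: 0.20 × 1 × 6.6 = 1.32 months, and 1.32/3.6 = 37%. Observed numbers are 86 × 0.7 = 60.2 and 86 × 0.9 = 77.4, so SE = 6.6·√(1/60.2 + 1/77.4) = 1.13 and bias/SE = 1.16. Under no true effect the rejection probability is 1 − Φ(1.96 − 1.16) + Φ(−1.96 − 1.16), about 21%.

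The sign depends on which arm loses more. Heavier loss of poor-outcome participants on active product flatters the product; heavier loss on placebo does the reverse. The 20% is an all-cause allowance, and the documents do not say how much of it this rule would cause. If the rule produces only part of the loss, its contribution to the bias is smaller.

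**4. The passages side by side.** Eligibility criteria and Intervention end participation after serious events or unblinding. Study setting and Advanced PD need the same people observed to week 36. The instruction to complete the assessments could mean one exit assessment or all remaining ones. An exit assessment cannot supply a later levodopa start date, nor the later OFF duration or PDQ-39 values.

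**The case against.** Several points on the other side stand.

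- **The mitigation is ambiguous and does not rule out later visits.** Sites must try to reach drop-outs and complete assessments. In a condensed article one can say only that the text does not clearly keep people on schedule.
- **A reader might infer that the groups analysed will not be those randomised.** The article does not say so. Counting someone as a drop-out is not the same as excluding them from analysis, and analysis sets are commonly left to the statistical analysis plan, which is not shown.
- **A reader might infer that mild-unit participants who leave for poor efficacy take the primary event with them.** That is voluntary withdrawal, a separate sentence from the persuasion rule, and a right that no amendment can remove. Therapy combination and Mild PD also let a worsening participant add levodopa while staying in the trial, and the date can be reported outside visits. Worsening therefore need not mean exit.
- **A reader might compute a large false difference in the mild unit.** Assume a 50% event risk and 86 × 0.20 = 17.2 lost per arm. If every lost placebo participant would have had the event, the observed placebo risk is (43 − 17.2)/68.8 = 37.5%, against 50% on active if loss there is unrelated to outcome. This charges the whole all-cause allowance to the rule and makes loss selective in one arm only. The same selectivity in both arms gives 37.5% in each and no difference. The event risk is itself an assumption, and the unit was sized on a difference in mean time.
- **Blinding with a matched placebo** makes differential exit less likely. It does not exclude it, since effects on symptoms or tolerability can still decide who leaves.

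None of this removes the instruction to persuade people to quit the study, or the end of research after unblinding.

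**Conclusion.** The point holds as a badly fixed rule, not as missing detail. Following the text as written loses outcome data for post-randomisation reasons in all three units, and in the advanced unit it conflicts with the outcomes chosen there. The loss is avoidable, and later analysis cannot undo it.

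Confidence is high on what the rule says and moderate on its consequence. Bias requires that leaving, or its relation to outcome, differs between arms, and the documents do not show that it will. The range from no bias to more than a third of the planned effect rests on assumed loss rates, assumed leaver–stayer differences and a comparison of observed outcomes only. Neither size nor direction can be derived from the documents. The amendment is still worth making, because it costs little and unrecorded outcomes may not be recoverable later.

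**What to change.** Amend the withdrawal paragraph in Eligibility criteria and the emergency-unblinding paragraph in Intervention as follows:

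1. Stopping the study product, for any reason including emergency unblinding, does not end outcome and safety follow-up.
2. Participants who do not withdraw consent keep the scheduled visits to week 60 (mild) or week 36 (moderate, advanced). Where visits are not possible, there is at least telephone contact for the unit's primary outcome: levodopa start date, OFF duration or PDQ-39.
3. They stay in their randomised group.
4. Poor compliance is deleted as a reason to leave the study.
5. The instruction to complete the assessments says which assessments and up to which week.

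Reconcile both paragraphs with the outcome list in Advanced PD, so that serious events are followed as outcomes and do not end observation. Clinical decisions on stopping the product are left unchanged.

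Cost: a protocol amendment, a letter to the seven sites, and extra contacts for up to about 20% of participants (0.20 × 412, about 82 people). The visits themselves are already scheduled.

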### Intervention

The three formulas are alternatives for the intervention differentiation among the groups. Ziyin Pingchan Decoction includes seven herbs and worms, namely, *Rehmanniae radix* praeparata (Shudihuang) 15 g, *Lycii fructus* (Gouqizi) 12 g, *Taxilli herba* (Sangjisheng) 15 g, *Gastrodiae rhizoma* (Tianma) 9 g, *Paeoniae radix* alba (Baishao) 15 g, *Bombyx batryiticatus* (Jiangcan) 9 g, and Scorpio (Quanxie) 3 g. Jiedu Pingchan Decoction is the Ziyin Pingchan Decoction with two additional herbs, namely, *Arisaematis rhizoma* preparatum (Zhitiannanxing) 15 g and *Curcumae rhizoma* (Ezhu) 9 g. Fuzheng Pingchan Decoction consists of Ziyin Pingchan Decoction and two extra herbs, namely, *Astragali radix* (Huangqi) 30 g and *Cistanches herba* (Roucongrong) 30 g. The doses of each herb and worm were determined according to The Chinese Pharmacopoeia (Ch. P) 2020 edition and fixed by clinical experience within a safe dose [26, 27].

The placebo will be made from maltodextrin and a 1/10 concentration of the corresponding decoction, which has no therapeutic effect [28]. The form, colour, smell, and solubility of the placebo will simulate the intervention medicine. The IMPs will be processed into granules by water extraction, separation, concentration, drying and granulation by Sichuan Neo-Green Pharmaceutical Technology Development Co., Ltd., and 8 g will be packed per sachet. The production and processing of the decoctions will be conducted in accordance with the Ch. P, and the processing and filling of the granules will be carried out in standardized clean production workshops. The dosage regimen is one package of granules in warm water twice a day, 30 min after breakfast and dinner. Every 56 sachets will be packed in a transparent package with a randomization code label for one month of treatment. Participants will be given the next 3 packages of IMPs at every follow-up visit. The last of the interventions will be 48 weeks for the mild PD unit and 24 weeks for the other 2 units. Participants will be asked to bring all leftover drugs to every follow-up visit to check their compliance.

If a serious adverse event or allergic reaction happens and is of concern relative to the research medication, the emergency envelope will be opened by the principal investigator of the centre. Once opened, research on that subject will be discontinued. Then, the time and reason for the emergency unblinding will be recorded in detail in the case report form (CRF). The patient will receive corresponding standardized treatment. Simultaneously, the relevant departments, including the ethics committees of each study centre, should be informed within 24 h.

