## Methods/design

### Study setting

This study is a multicentre, randomized, double-blind, placebo-controlled clinical trial. The study will be simultaneously carried out in seven centres in China, including Longhua Hospital Affiliated to Shanghai University of Traditional Chinese Medicine, Xinhua Hospital Affiliated to Shanghai Jiao Tong University Medical College, Shuguang Hospital Affiliated to Shanghai University of Traditional Chinese Medicine, No 1 People’s Hospital Affiliated to Shanghai Jiao Tong University Medical College, Yueyang Hospital of Integrated Traditional Chinese and Western Medicine affiliated to Shanghai University of Traditional Chinese Medicine, Ruijin Hospital Affiliated to Shanghai Jiao Tong University Medical College, and Yangzhi Rehabilitation Hospital Affiliated to Tongji University. This study is divided into 3 substudies. PD patients diagnosed at different stages will be screened into different units: mild PD unit, moderate PD unit, and advanced PD unit. The mild PD unit will receive a 48-week therapy and 12-week follow-up, and face-to-face assessments will be conducted at baseline (week 0), week 12, week 24, week 36, week 48, and week 60. The other two units will receive a 24-week therapy and 12-week follow-up, and face-to-face assessments will be conducted at baseline (week 0), week 12, week 24, and week 36. Recruitment for the study will be launched in April 2022 and it is anticipated to finish before July 2024. The flow chart of the trial is shown in Fig. 2.

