### Safety outcomes

Safety outcomes will be assessed at baseline and at the last visit, including red blood cell count (RBC), white blood cell count (WBC), platelet count (PLT), glutamic oxaloacetic transaminase (GOT), glutamic pyruvic transaminase (GPT), serum creatinine (Scr) and electrocardiogram (EKG). Laboratory results will be judged as abnormal if 20% out of the normal range or with supportive signs or symptoms. The WBC and EKG results should be judged based on the patient's specific situation.

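### The emergency unblinding rule opens the code on suspected drug-relatedness alone and then ends research on the subject, in tension with the protocol's own drop-out follow-up

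*Protocol article*

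**What the plan says.** The emergency unblinding paragraph at the end of the Intervention section of the protocol article gives a complete rule.

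- **Trigger:** "If a serious adverse event or allergic reaction happens and is of concern relative to the research medication, the emergency envelope will be opened". The centre's principal investigator opens it.
- **Consequence:** "Once opened, research on that subject will be discontinued". The time and reason go into the case report form, the patient receives standard treatment, and the ethics committees are told within 24 h.

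Three other places bear on it.

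- **Withdrawal paragraph, Eligibility criteria:** "Subjects with poor compliance, serious comorbidities or complications, or serious adverse events will be persuaded to quit the study". These subjects count as drop-outs, and for drop-outs "investigators should try to contact the subject as much as possible to inquire about the reason and complete the assessments".
- **Safety outcomes:** "Safety outcomes will be assessed at baseline and at the last visit". The tests are three blood counts, two transaminases, serum creatinine and an electrocardiogram. The schedule of assessments (Table 2) shows no safety tests in between.
- **Intervention, composition of the placebo:** "The placebo will be made from maltodextrin and a 1/10 concentration of the corresponding decoction, which has no therapeutic effect".

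**The concern.** Breaking the code for one participant is normally reserved for cases where knowing the allocation would change that participant's care. Here the trigger is only that the event is thought to be related to the product. A mild rash attributed to the granules would qualify. The treatment that follows is not described as depending on which arm is revealed.

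The consequence is also broader than it needs to be. Suspected drug harm is a reason to stop the product. It is not in itself a reason to stop observing the subject. Taken literally, the sentence stops research altogether, in the subjects whose safety and outcome data matter most for judging the product. A site would also hold two instructions that pull apart: discontinue research after opening, and try to complete assessments after drop-out.

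**Working it through.** The plan gives no figure to reproduce, and no event rate is available. The check compares the stated rules and then counts what one affected subject could lose.

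**Step 1. Is the arm needed for care?** The rule does not ask. For suspected toxicity, the active product has ten times the decoction concentration of the placebo, so knowing the arm may help and opening may be justified. For allergy, the placebo carries one tenth of the same decoction, so learning that a subject is on placebo does not rule out exposure. That does not prove the arm irrelevant in every allergic reaction. It does mean that opening by default has less to offer.

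**Step 2. What does the rule add to the withdrawal paragraph?**

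| Subject | Withdrawal paragraph already says | Unblinding paragraph adds |
|---|---|---|
| Serious adverse event, suspected drug-related | Persuaded to quit; treated as drop-out; try to complete assessments | Mandatory opening; literal end of research, which conflicts with completing assessments |
| Non-serious allergic reaction, suspected drug-related | Not on the list of those persuaded to quit | Mandatory opening; the discontinuation itself; doubt about follow-up |

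**Step 3. The most one subject could lose.** Visits come from Study setting. In the mild unit, "face-to-face assessments will be conducted at baseline (week 0), week 12, week 24, week 36, week 48, and week 60", which is 5 post-baseline visits. In the other two units, "face-to-face assessments will be conducted at baseline (week 0), week 12, week 24, and week 36", which is 3. For an illustrative event just after week 12, with research ended:

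- mild unit: 5 − 1 = 4 of 5 post-baseline visits lost (weeks 24, 36, 48, 60), or 60 − 12 = 48 weeks of observation;
- moderate and advanced units: 3 − 1 = 2 of 3 lost (weeks 24, 36), or 36 − 12 = 24 weeks.

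The safety tests have 2 scheduled time points, hence 2 − 1 = 1 post-baseline panel, made up of 7 tests.

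**Step 4. How the readings change this.**

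| Reading | Post-baseline safety panel |
|---|---|
| Research ends literally, and the last visit is the final scheduled one | 0 of 1 obtained |
| Research ends, but the last visit is the subject's own last visit | can be obtained, up to 1 of 1 |
| Drop-out instruction applied after opening | up to 1 of 1 obtained |

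The visit losses in Step 3 likewise shrink, possibly to zero, if the drop-out instruction is followed. For serious adverse events, part of those losses would arise from the persuaded-to-quit rule anyway, so they are not the increment due to the unblinding rule.

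**The case against.** The strongest reply is that the two paragraphs can be read together. A subject whose research is discontinued is naturally a drop-out, and the drop-out instruction already asks for assessments to be completed. On that reading the data loss largely disappears. The trigger also needs a judgement that the event is of concern relative to the product, it governs an emergency envelope, and prompt knowledge of the arm when harm is suspected is a defensible preference. Finally, a condensed article may leave unscheduled tests at an event, and other detail of the code-break procedure, to the full protocol.

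Much of this stands. The harmonising reading is possible, and nothing is held here against the absence of post-event testing from the article. It does not rescue the rule as stated. The opening is unconditional in the text on any reading of follow-up, the unblinding paragraph does not refer to the drop-out instruction, and non-serious allergic reactions are brought into discontinuation by this paragraph alone.

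Three stronger readings are tempting and are not supported:

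- **The rule loses the only post-baseline safety panel in subjects with suspected harm.** This needs two unfavourable readings at once, as Step 4 shows, and the text compels neither.
- **The loss is unequal between arms and biases the comparison.** Events might be more frequent on the full-strength extract, but the documents give no rates, so this is conjecture.
- **Opening one envelope compromises the ratings of other participants.** The Randomization section keeps enrolling and evaluating researchers blinded, and nothing shows that a revealed arm reaches them.

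**Conclusion.** The point holds as a defect in a stated rule. The code must be opened for any serious adverse event or allergic reaction suspected to be drug-related, with no need-for-care condition and no severity threshold for allergy, and research on that subject is then ended. For serious adverse events the increment is mainly an avoidable unblinding and an instruction that sits badly with the drop-out follow-up. For non-serious allergic reactions it also includes the discontinuation.

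The number of subjects affected is unknown and may be small. The counts in Step 3 are an upper limit per subject for one chosen event time, and they assume that the drop-out instruction is not applied. Actual loss may be near zero. The case for changing the text is that better wording is cheap, not that a large loss has been shown. The unblinding part does not depend on how follow-up is read.

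**What to change.** In the emergency unblinding paragraph of the Intervention section:

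1. State that the study product is stopped under blind and the event is reported with the code sealed.
2. State that the envelope is opened only when the treating physician needs the allocation to manage the participant.
3. Replace "Once opened, research on that subject will be discontinued" with wording such as: *study product is stopped and the remaining assessments, including the safety tests listed under Safety outcomes, are completed where possible, as for drop-outs under Eligibility criteria*.

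The cost is two or three sentences of protocol text. Emergency access to the code is kept. The downside is that some suspected events will be managed at the centre without the arm being known.
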